### Aim 2 analyses

Aim 2 compares the effect of HELM vs. educator coaching on RUBIES sustainment as measured by BSPI scores (arm 1 vs. arm 2). The hypothesis states that intervening with HELM will induce better sustainment (i.e., higher RUBIES fidelity) in Year 2 at Week 52 and Week 76 compared to educator coaching only. The two observations of sustainment for each educator (paired 1:1 with a child) in Year 2 are nested within the educator, who is nested within a school. For this outcome, we will fit an LMM with the following hierarchical structure: the Level 1 model (observation) will include Week 52 and Week 76 fidelity observations for each educator. This level does not include a growth model because we do not assume fidelity will systematically increase or decrease during the sustainment school year; instead, we assume random fluctuation around an educator mean for the year. At Level 2 (educator), we will include a random intercept and educator-level covariates such as years of experience which may be a potential confounder. Covariates will be selected as described above. At Level 3 (school), we will include a random intercept and a treatment assignment indicator (RUBIES + HELM vs. RUBIES only) which will be contrast coded to facilitate main effect interpretations. The coefficient for the treatment assignment indicator in this model will test whether RUBIES sustainment (i.e., level of RUBIES fidelity in the second year of study enrollment) was superior for educators assigned to RUBIES + HELM compared to educators assigned to RUBIES only at Week 52 and Week 76. As a secondary implementation outcome, we will analyze a binary indicator of RUBIES sustainment at Week 52 and Week 76 (based on the CGI-S) to evaluate whether HELM improved the odds of sustaining RUBIES at a provisional ‘sustainment’ cutoff. This analysis will use a similar model as Aim 2, but data from different timepoints or distributions (LMM and Generalized LMM for binary outcomes).

Aim 3 involves mediation analysis to evaluate the mechanisms that link RUBIES to children’s externalizing behavior and HELM to RUBIES sustainment as measured by the BSPI. The primary focus will be testing the main effects of RUBIES on the hypothesized mediator, children’s self-management skills, and of HELM on its hypothesized mediators, implementation leadership and climate, in order to establish the discriminant effects of these exposures relative to their comparators. Following these primary analyses, exploratory analyses will be used to test the remainder of the mechanistic chain proposed by RUBIES. These analyses will use the product of coefficients approach to mediation and will build on the foundational Aim 1 model [63–66]. The same approach will be used for the HELM mediators, using the model for Aim 2 as the foundational model. Consistent with best practices, we will conduct robustness checks and sensitivity analyses regarding the sequential ignitability assumption and other assumptions of our mediation analyses following model estimation [67].

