**Methods:**

In a cluster-randomized, hybrid type 2 effectiveness-implementation trial, schools will be randomized to one of 3 arms: 1) educator coaching in RUBIES and school participation in HELM; 2) educator coaching in RUBIES only; or 3) a control condition incorporating an active clinical comparator, educator psychoeducation. We will enroll 42 schools and 126 educators yoked to 126 elementary-aged autistic children. Depending on arm, educators will complete study instruments up to six times: 1) Spring semester prior to the year of school and student enrollment (implementation baseline; arms 1–2); 2) Fall semester Year 1 (clinical baseline; arms 1–3); 3) 16 weeks (arms 1–3); 4) 24 weeks (arms 1–3); 5) 52 weeks (arms 1–2); and 6) 76 weeks (arms 1–2). The primary clinical outcome compares arms 1 & 2 vs. 3 on change in autistic children’s externalizing behavior from clinical baseline to 24 weeks. The primary implementation outcome compares arms 1 vs. 2 on RUBIES sustainment, operationalized as educators’ average RUBIES fidelity at 52 and 76 weeks.

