**URL of trial registry record**

https://clinicaltrials.gov/study/NCT07276750?cond=Autism&intr=RUBIES&rank=1.

Contributions to the literature
Sustainment of evidence-based practices in schools is challenging given the implementation cliff that occurs oversummer break in-between school years. This study will simultaneously evaluate the clinicaleffectiveness of a promising, relatively low-cost, and highly feasible intervention that addressesexternalizing behavior in autistic students, called RUBI in Educational Settings (RUBIES), and theimplementation effectiveness of a promising leadership-focused implementation strategy calledHelping Educational Leaders Mobilize evidence (HELM), in public elementary schools.The proposed trial will generate evidence regarding the clinical effectiveness of RUBIES which fills agap in educator-delivered interventions that meaningfully support autistic youth throughout theschool day to minimize externalizing behaviors.Leadership-focused implementation strategies have shown promise for improving fidelity in othersettings; however, their effects on sustainment and in public schools remains unexamined. Theproposed trial tests whether the addition of HELM improves sustainment of evidence-based practicesin public elementary schools beyond educator coaching alone.If successful, this study will have substantial public health impact because it will produce an effectiveintervention for a prevalent problem among a high impact population and will determine how tosustain this (and other) intervention(s) with high fidelity.

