## Method

### Study design

This study will use a hybrid type 2 effectiveness-implementation trial with HELM, RUBIES, and a psychoeducation only control condition to provide a rigorous test of the effects of RUBIES and HELM across 126 educators paired with 126 autistic children in 42 elementary schools. The full sample of 42 elementary schools will be enrolled in three cohorts of approximately 14 schools each nationwide. Each cohort will participate for two years. Depending on arm, educators will complete study instruments up to six times: 1) Spring semester prior to the year of school and student enrollment (implementation baseline; arms 1–2); 2) Fall semester Year 1 (clinical baseline; arms 1–3); 3) 16 weeks (arms 1–3); 4) 24 weeks (arms 1–3); 5) 52 weeks (arms 1–2); and 6) 76 weeks (arms 1–2). Leaders and educators will be compensated $40 at implementation and clinical baseline, $50 at Week 16, $60 at Week 24, $70 at Week 52, and $80 at Week 76 for the completion of study instruments at each timepoint. See Fig. 3 for study design.

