## Clinical interventions

### Rubies

RUBIES is a manualized, 9-session educator-delivered intervention that addresses externalizing behaviors in autistic children [45, 46]. Although RUBIES follows a standardized manual, behavioral strategies are tailored to the autistic student, informed by target behaviors and their hypothesized function, as well as child- and educator-specific classroom needs. One goal of RUBIES is for educators to build mastery over a set of behavioral skills that are used to support the student currently under their care with potential to generalize to other autistic students in their classrooms. RUBIES also focuses on engaging the student’s broader educational team through an initial collaborative planning session as well as targeted goals in every session focused on activating a weekly team communication and generalization plan. Sixteen weeks will be allotted to complete the 9 modules, to account for cancellations, scheduling conflicts, holidays, etc. Educators will receive a RUBIES workbook, access to an online platform that houses resources (e.g., extra copies of activity sheets, video models of an educator implementing RUBIES strategies), and a toolkit with recommended sensory tools and premade visual supports to accompany RUBIES use. Educators will engage in RUBIES sessions with a coach who has a master’s degree or higher and completed training to fidelity in RUBIES (i.e., manual review, viewing of RUBIES sessions, co-leading sessions with a certified RUBIES-trainer). The coach will facilitate weekly hour-long RUBIES sessions with educators via Zoom at a convenient time. Coaching sessions will include a practice plan review, didactic instruction on behavioral strategies, and coaching and consultation to tailor newly learned strategies. Educators will be offered a Booster session at three time points during Year 02. Booster sessions will involve reviewing three main components of RUBIES: conducting a functional assessment, prevention strategies, and how to implement more effective responses to challenging behaviors.

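### The Aim 2 model has no term for Week 52 versus Week 76; a fixed week effect would protect the HELM contrast at almost no cost, although the likely bias is small

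*Protocol article*

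**What the plan says.** The abstract defines the primary implementation outcome as RUBIES sustainment, "operationalized as educators’ average RUBIES fidelity at 52 and 76 weeks", compared between arm 1 (RUBIES + HELM) and arm 2 (RUBIES only).

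The Aim 2 analyses section sets out a three-level linear mixed model. Level 1 holds the two Year 2 ratings per educator. On time, the section says: "This level does not include a growth model because we do not assume fidelity will systematically increase or decrease during the sustainment school year". The working assumption that takes the place of a time trend is worded like this: "instead, we assume random fluctuation around an educator mean for the year". Level 2 has an educator random intercept and covariates. At Level 3, "we will include a random intercept and a treatment assignment indicator (RUBIES + HELM vs. RUBIES only"), with the arm contrast coded. No term for visit is listed at any level.

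Other parts of the protocol bear on this:
- Rubies section: "Educators will be offered a Booster session at three time points during Year 02". The boosters belong to RUBIES, so both Aim 2 arms are offered them. Their timing relative to Weeks 52 and 76 is not given.
- Sample size and power: 25% educator attrition and a within-person correlation of 0.3. Attrition is not split by arm or visit.
- Table 1 places both Week 52 and Week 76 in Year 2.

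**The concern.** Having no reason to expect a rise or fall is a reason to leave the Week 76 mean free. Omitting the term instead fixes the difference between the visit means at exactly zero. If every educator supplied both ratings this would not matter for the arm contrast, because a shift common to both arms would cancel. It stops cancelling when the arms differ in the proportion of educators who have a Week 76 rating. The arm that keeps more of those ratings then carries more of the shift, and the model has nowhere to put it except the arm coefficient.

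At stake is the primary implementation test. It could pick up a small HELM effect, in either direction, from retention alone. With missing visits and a shift, the coefficient would also no longer compare like with like on the average of the two weeks, which is how the outcome is defined.

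**Working it through.** **Inputs from the protocol (Sample size and power):** 42 educators per arm in 28 schools in total, so 3 per school; d = 0.76 (0.13 / 0.17 = 0.765); alpha 0.05, taken as two-sided; 10% for clustering; 25% attrition; within-person correlation r = 0.3.

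**Assumed, because the protocol does not give them:** the size of the visit shift; Week 76 retention by arm; every educator observed at Week 52; Week 76 loss completely at random within arm; and variance components of 0.1 (school), 0.2 (educator) and 0.7 (residual), which reproduce r = 0.3.

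**Step 1: the plan's own figure.** Effective n per arm = 42 × (1 − 0.25) / [1 + (3 − 1) × 0.10] = 31.5 / 1.2 = 26.25. With one observation per educator, power is 78.6% for d = 0.76 and 79.1% for 0.13 / 0.17. The stated 80% is reproduced to within 2 points.

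**Step 2: how much of the shift each arm carries.** Without a visit term, an educator with both ratings contributes a mean that contains half the shift. Its variance factor is (1 + 0.3) / 2 = 0.65, so its weight is 1 / 0.65 = 1.538. An educator with Week 52 only contributes none of the shift and has weight 1. With Week 76 retention p, the arm carries the fraction

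share(p) = p × 1.538 × 0.5 / [p × 1.538 + (1 − p)]

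- p = 0.85: 0.654 / 1.458 = 0.449
- p = 0.65: 0.500 / 1.350 = 0.370
- Difference: 0.078 of the shift

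**Step 3: spurious HELM effect, in SD units.** Each retention pair averages 75%, in line with 25% attrition.

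| Week 76 retention, arm 1 / arm 2 | Fraction of shift | Shift 0.5 SD | Shift 1 SD |
|---|---|---|---|
| 75% / 75% | 0 | 0 | 0 |
| 80% / 70% | 0.039 | 0.020 | 0.039 |
| 85% / 65% | 0.078 | 0.039 | 0.078 |
| 90% / 60% | 0.117 | 0.059 | 0.117 |

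The sign reverses if the shift is downward or if arm 2 keeps more ratings. With r = 0.6 the 85% / 65% fraction rises only to 0.089.

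**Step 4: simulation.** 28 schools × 3 educators, no true HELM effect, 20,000 runs per scenario, variance components treated as known.

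| Retention, shift | Bias without / with week term | SE without / with | Rejection rate without / with |
|---|---|---|---|
| 75% / 75%, 0.5 SD | −0.003 / −0.003 | 0.208 / 0.207 | 4.1% / 4.0% |
| 85% / 65%, 0.5 SD | 0.041 / 0.001 | 0.209 / 0.209 | 4.5% / 4.1% |
| 85% / 65%, 1 SD | 0.077 / −0.001 | 0.212 / 0.209 | 5.6% / 4.0% |
| 90% / 60%, 1 SD | 0.117 / −0.001 | 0.212 / 0.209 | 7.6% / 4.0% |

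The simulation agrees with the formula. A week term removes the bias with no visible loss of precision.

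**Step 5: scale.** 0.039 / 0.76 is about 5% of the design effect, and 0.039 / 0.209 is about one-fifth of a standard error. In the extreme case, 0.117 / 0.76 is about 15%.

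**The case against.** The strongest reply is that the omission is deliberate and reasoned. The outcome is an average over two visits in one school year, and a model built around an educator mean suits that. Neither ingredient of the bias is documented. One overall attrition figure is given, and educators who leave before Week 52 are missing at both visits and cause no leak. Boosters offered to both arms fit stable fidelity as well as they fit a shift. All of this stands, and it is why the point is minor. It does not make the zero constraint necessary, because the averaged target can be kept with the week left free.

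Three stronger readings are tempting, and the protocol does not support them.

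- **That the summer break makes a shift likely.** The contributions list speaks of an "implementation cliff that occurs oversummer break in-between school years". Weeks are counted from the clinical baseline ("Fall semester Year 1 (clinical baseline; arms 1–3")), and both sustainment visits fall in Year 2. The cliff therefore comes between Week 24 and Week 52, before both visits. A later rebound or further decline is conceivable, but nothing in the protocol states one.
- **That 25% attrition implies unequal loss by arm.** HELM acts on leadership and climate, so equal retention cannot be taken for granted, but a gap is an assumption.
- **That the model fails Hypothesis 2 because it gives no separate result at each week.** The primary outcome is defined on the average. By-visit estimates would need an arm-by-week term, and an article may leave those to the analysis plan.

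**Conclusion.** The point holds as a minor robustness issue. The Aim 2 model constrains the Week 52 and Week 76 means to be equal, and the stated reason does not require that constraint. Bias in the HELM coefficient needs both a common visit shift and arm-unequal Week 76 loss. In a moderate scenario (0.5 SD, 85% versus 65%) it is about 0.04 SD with type I error essentially unchanged, and with equal loss it is zero. Only an extreme combination (1 SD, 90% versus 60%) gives a bias of 0.117 SD and a rejection rate of 7.6% instead of 4.0%. The shift, the retention gap and the variance split between school and educator are assumptions, and the simulation treats the variance components as known. Nothing here shows that the planned result would be seriously wrong.

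**What to change.** Add a fixed effect for week (52 versus 76) to the Aim 2 linear mixed model, and keep the arm coefficient across the two visits as the primary test, in line with the average-fidelity definition in the abstract. One sentence in the Aim 2 analyses section is enough. The cost is one degree of freedom, with the standard error essentially unchanged at about 0.21 SD. The Discussion states that no participants had been enrolled as of February 2026, so the change can be prespecified cleanly.

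For consistency the same term can go into the generalized model for the binary CGI-S outcome, although its behaviour there was not simulated. Arm-by-week estimates are optional supportive output.

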### Hypothesis 3b

Increases in principal implementation leadership and school implementation climate will mediate HELM’s effect on educator sustainment relative to RUBIES coaching alone (arm 1 vs. arm 2).

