#### HELM mediators

Educators will complete the School Implementation Leadership Scale (S-ILS) [55], a 21-item measure that assesses seven subscales of implementation leadership: knowledgeable (understanding of RUBIES and implementation issues), supportive (support for RUBIES use), proactive (anticipating and addressing challenges), perseverant (consistent and responsive to challenges), communicative (shares implementation related information with staff), has a vision/mission (oriented towards using RUBIES), and available in implementing RUBIES [5, 37]. The S-ILS is a psychometrically validated and reliable instrument (α = 0.95–0.98). Implementation leadership scores are generated for a school at each timepoint (implementation baseline, Weeks 16, 24, 52, and 76) by aggregating individual educator ratings to the school level.

Educators also will complete the School Implementation Climate Scale (S-ICS) [56], a 21-item measure that assesses seven subscales of implementation climate: focus, educational support, recognition, rewards, use of data, existing supports, and RUBIES integration [37, 56]. The S-ICS is a psychometrically validated and reliable instrument (α = 0.81–0.91; 39, 79). Implementation climate is scored by aggregating individual educator ratings to the school level.

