### Aim 1 analyses

Aim 1 evaluates the main effect of RUBIES vs. educator psychoeducation on child externalizing behavior among children in Year 1 of study enrollment. The primary outcome for this comparison is change in child externalizing behavior from baseline to Week 24, contrasting all groups assigned to RUBIES vs. educator psychoeducation (i.e., arms 1 & 2 vs. arm 3). We will fit a three-level Linear Mixed Model (LMM) as follows: the Level 1 model (piece wise time) with a “knot” (i.e., inflection point) at Week 16 used to capture each child’s change in externalizing behavior from Baseline to Week 16, and potentially different slope from Week 16 to Week 24. At Level 2 (child/educator; due to 1:1 pairing), each growth parameter will be modeled as a function of an intercept and child/educator-level covariates. We will select covariates by testing for differences across arms on youth and educator characteristics; covariates will be included if the effect size ≥|0.2|. At Level 3 (school), we will include a random intercept to account for the nesting of the child-educator dyads within schools and a treatment assignment indicator ([RUBIES + HELM] + [RUBIES only] vs. educator psychoeducation). We will test the interaction effect of treatment condition with time. Linear combinations of the growth parameters from this model will be used to test whether improvement in child externalizing behavior was superior for autistic children assigned to [RUBIES + HELM] + [RUBIES only] vs. educator psychoeducation from Baseline to Week 24.

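### HELM mediation (H3b): the stated base model and covariate rule give the Year 0 leadership and climate scores no analytic role, which costs precision and leaves the exploratory mediator-to-fidelity path open to confounding

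*Protocol article*

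**What the plan says.** Hypothesis 3b is worded as change: "Increases in principal implementation leadership and school implementation climate will mediate" the effect of HELM on sustainment. Both mediators are school-level aggregates of educator ratings. The HELM mediators section states: "Implementation leadership scores are generated for a school at each timepoint (implementation baseline, Weeks 16, 24, 52, and 76". Table 1 marks the same time points for S-ILS and S-ICS, starting in Spring Year 0, for the two RUBIES arms. The HELM section places the leaders' initial training in the summer, after that survey.

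The Aim 3 paragraph, which follows the Aim 2 analyses without its own heading, makes the treatment-to-mediator effects the primary focus and the rest of the chain exploratory. It names the product of coefficients approach built on the Aim 1 model for RUBIES. For HELM it says: "The same approach will be used for the HELM mediators, using the model for Aim 2 as the foundational model".

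The Aim 2 model is described as follows:
- Observations: "the Level 1 model (observation) will include Week 52 and Week 76 fidelity observations for each educator".
- Time: "This level does not include a growth model because we do not assume fidelity will systematically increase or decrease during the sustainment school year".
- Educator level: "we will include a random intercept and educator-level covariates such as years of experience which may be a potential confounder".
- School level: a random intercept and the treatment indicator.
- Covariate choice: as in Aim 1, where the rule reads "We will select covariates by testing for differences across arms on youth and educator characteristics; covariates will be included if the effect size ≥|0.2|".

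The Aim 3 paragraph also commits to robustness checks and sensitivity analyses on the mediation assumptions.

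**The concern.** The RUBIES mediation builds on a model that contains the baseline. The HELM mediation builds on the one model that has none. The covariate rule does not fill the gap, for two reasons. Its pool is youth and educator characteristics, so a school-level mediator score is outside it. It also acts only when the arms differ, and that is the wrong trigger for the mediator-outcome path. Randomization protects the comparison of arms. It does not protect the comparison of schools with high and low later leadership. A school that was well led before HELM may have both better leadership later and better fidelity later, and this holds even if the arms are perfectly balanced at Year 0.

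Two things are at stake. The HELM-to-mediator test, a primary focus of Aim 3 with only 28 schools, gives up precision that the trial has already paid for; the power section gives no figure for it. The indirect effect could also appear positive when leadership and climate do nothing for sustainment.

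**Working it through.** **Inputs from the Protocol article.** 28 schools (14 per arm), 3 educators per school, Type-I error 0.05 (two-sided assumed), 10% clustering, correlation 0.3 between the two fidelity ratings. **Assumed, because the article does not give it:** the school-level correlation ρ between Year 0 and follow-up mediator scores, shown from 0.2 to 0.7.

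**Plan's own figure for the base model.** Aim 2 states 80% power for a difference of 0.13 with SD 0.17 (d = 0.76). After 25% attrition n = 42 × 0.75 = 31.5 per arm, and the design effect is 1 + (3 − 1) × 0.10 = 1.2. SE = 0.17 × √(2 × 1.2 / 31.5) = 0.0469. Then 0.13 / 0.0469 = 2.77, and power = Φ(2.77 − 1.96) = 79%. This agrees with 80% when the two ratings are counted as one. There is no stated figure for the HELM mediators to reproduce.

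**Step 1: HELM to mediator.** For a school-level mediator, power comes from a noncentral t with noncentrality (d / f) × √(14/2).
- Follow-up score only: f = 1, 26 df.
- Adjusted for Year 0 (ANCOVA): f = √(1 − ρ²), 25 df.
- Change score: f = √(2(1 − ρ)), 26 df.

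Without Year 0, 80% power needs d = 1.10, and power at d = 0.9 is 63%.

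| ρ | f (ANCOVA) | d for 80% power, ANCOVA | Power at d = 0.9, ANCOVA | d for 80% power, change score |
|---|---|---|---|---|
| 0.2 | 0.98 | 1.08 | 65% | 1.39 |
| 0.3 | 0.95 | 1.05 | 67% | 1.30 |
| 0.5 | 0.87 | 0.95 | 75% | 1.10 |
| 0.6 | 0.80 | 0.88 | 82% | 0.98 |
| 0.7 | 0.71 | 0.79 | 89% | 0.85 |

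A change score does worse than the follow-up score alone when ρ is below 0.5. A large-sample simulation with a true HELM effect of 0.76 SD gave 0.760 for follow-up level, change and ANCOVA alike, so leaving out Year 0 does not bias this step.

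**Step 2: mediator to fidelity.** Let follow-up leadership be aT + ρM0 + error with unit variance within arm, where T is the arm and M0 the Year 0 score. Let fidelity depend on M0 with coefficient c (SD of BSPI per SD of M0) and not on later leadership, so the true b = 0. Leaving out M0 gives an expected b of c × ρ and a spurious indirect effect of a × c × ρ.
- a = 0.76, ρ = 0.5, c = 0.2: b = 0.10 and indirect effect 0.076. The large-sample check gave b = 0.10 without M0 and 0.00 with it.
- a = 1.0, ρ = 0.6, c = 0.2 to 0.3: indirect effect 0.12 to 0.18.

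**Step 3: false positives.** Simulated trials with 28 schools, 3 educators each, a HELM shift of 1.0 SD and c = 0.2 to 0.3. A false positive is joint significance of both paths when the true indirect effect is zero.

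| ρ | Without Year 0 | With Year 0 |
|---|---|---|
| 0.2 to 0.3 | about 5% to 7% | about 4% to 5% |
| 0.5 | 9% to 17% | about 4% to 5% |
| 0.6 | 12% to 23% | about 4% to 5% |

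The last column assumes that the Year 0 score is itself the confounder. If instead an unmeasured stable school trait drives Year 0 leadership, later leadership and fidelity (ρ = 0.6, same effect sizes), adjustment lowers false positives from 21% to 36% down to 10% to 15%.

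**The case against.** The strongest reply is that this is a condensed article and baseline adjustment is ordinary content for an analysis plan. No HELM mediator equation is written out. The Aim 2 model has fidelity as its outcome, so it cannot itself be the HELM-to-mediator equation, and a foundational model leaves room for added terms. Table 1 labels the S-ILS and S-ICS rows as HELM mediators with Year 0 included. A reader might infer that the Year 0 scores will go unused and that increases will be tested as raw levels. The article does not say so, and the scores are in any case used for HELM feedback. That part of the reply stands: the supportable statement is that no analytic role is given. It does not remove the point, because the article goes beyond silence. It names a base model and a covariate rule, and neither reaches these scores.

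A second reply is that under randomization a difference in follow-up levels estimates the same HELM effect as a difference in increases. This stands too: the first path loses precision, not validity.

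Third, the path open to confounding is exploratory and sensitivity analyses are planned. Both are true and limit the consequence. Sensitivity analysis probes what cannot be measured, however; it does not replace adjusting for a candidate confounder that has been measured.

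Fourth, ρ may be low. Schools must have no previous RUBIES exposure, yet the Year 0 ratings concern RUBIES-specific leadership. At ρ of 0.2 to 0.3 the gain is 2 to 4 points of power at 0.9 SD, and false positives stay close to nominal.

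**Conclusion.** The point holds as a cheap improvement to the HELM mediation. Aims 1 and 2 are unaffected. On the primary HELM-to-mediator test the stated plan is unbiased but less precise. The loss at 0.9 SD runs from 2 points of power (ρ = 0.2) to 26 points (ρ = 0.7). On the exploratory path the risk of a false indirect effect runs from negligible at low ρ to 12% to 23% at ρ = 0.6, provided that Year 0 leadership or climate has its own effect of 0.2 to 0.3 SD on later fidelity. Neither ρ nor that effect is in the article, so these are ranges and not predictions.

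A reader might also infer that the planned test of H3b is invalid, or that adjustment would fully cure the confounding. Neither follows. The arm comparison is protected by randomization, and adjustment helps only partly if an unmeasured school trait is the source.

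**What to change.** Add to the Aim 3 paragraph: the HELM mediator models, and the BSPI model used for the mediator-outcome path, will each include the school's Year 0 S-ILS (or S-ICS) score as a covariate, irrespective of balance between arms. Use the ANCOVA form and not a change score. Keep the planned sensitivity analyses on sequential ignorability as a supplement.

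The cost is one sentence and one degree of freedom per model. The scores are already scheduled in both arms, and the article reports no enrolment as of February 2026, so the choice can still be fixed before any data exist.
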